#### Control group

3.6.2

The control group will receive standardized usual care. Participants in the control group will receive health education and symptom-oriented management once weekly for 8 weeks, with each session lasting approximately 40 min. The program will cover balanced diet, sleep hygiene, stress management, psychological support, and tailored symptom management advice when clinically indicated. To reduce contamination, additional interventions specifically targeting fatigue, such as newly initiated pharmacotherapy, acupuncture, or herbal prescriptions, will not be permitted during the 8-week treatment period unless deemed clinically necessary. Stable pre-existing medications may be continued. Standardized usual care will be delivered by two TCM attending physicians who are licensed clinicians and have completed study-specific training and Good Clinical Practice certification. Concomitant medications and any rescue treatments will be recorded at each visit. Staff qualifications, training records, and adherence to the intervention protocol will be documented and audited.

Participant blinding is not feasible because of the nature of the Tuina intervention. The control group will receive health education and symptom-oriented management with standardized contact procedures and approximately matched total contact time, which is intended to help reduce imbalances in attention and trial engagement between groups. However, because treatment frequency and tactile contact cannot be matched, residual differences in treatment expectancy and performance effects may remain. This comparator was chosen to reflect current clinical management for CFS, in which symptom-oriented and supportive care remains the predominant non-pharmacological management approach. The study therefore evaluates standardized Tuina in comparison with standardized usual care, rather than against an inert, no-treatment, or fully attention-matched sham condition.

### Outcomes

3.7

#### Primary outcome

3.7.1

The primary outcome is fatigue severity, assessed as the change in Fatigue Scale-14 (FS-14) total score from baseline to week 8. The FS-14 is a patient-reported instrument comprising two domains: physical fatigue (items 1–8) and mental fatigue (items 9–14) (Chalder et al., 1993). Items 10, 13, and 14 are reverse-worded and will be recorded according to the scoring manual so that higher scores indicate greater fatigue. For the primary analysis, binary scoring (0–1 per item) will be used, yielding a total score ranging from 0 to 14, with subscale scores ranging from 0 to 8 for physical fatigue and 0 to 6 for mental fatigue. The FS-14 has demonstrated acceptable validity and reliability in Chinese populations (Wang et al., 2000). It will be administered at baseline, week 4, week 8, and at follow-up visits at weeks 12 and 24 post-treatment. Participants will complete the questionnaire with reference to their experience during the preceding week.

FS-14 was selected as the primary outcome because fatigue severity remains the most clinically prominent and pragmatically measurable symptom domain in CFS trials. Post-exertional malaise, a core clinical feature of CFS, will be further assessed at baseline using the DePaul Symptom Questionnaire–Post-Exertional Malaise (DSQ-PEM) as part of participant characterization.

#### Secondary outcomes

3.7.2

Health-related quality of life will be assessed using the 36-Item Short Form Health Survey (SF-36) (Ware and Sherbourne, 1992). The SF-36 covers eight domains: physical functioning, role physical, bodily pain, general health, vitality, social functioning, role emotional, and mental health. Each domain score will be transformed to a 0–100 scale, with higher scores indicating better health status.

Sleep quality will be assessed using the Pittsburgh Sleep Quality Index (PSQI) (Buysse et al., 1989). The PSQI includes 19 self-rated items that generate seven component scores: subjective sleep quality, sleep latency, sleep duration, habitual sleep efficiency, sleep disturbances, use of sleep medication, and daytime dysfunction. The global score ranges from 0 to 21, with higher scores indicating poorer sleep quality.

Pain intensity will be assessed using a 10-cm visual analog scale (VAS) (Hawker et al., 2011), ranging from 0 (no pain) to 10 (worst imaginable pain), with higher scores indicating greater pain intensity.

Anxiety and depressive symptoms will be assessed using the Self-Rating Anxiety Scale (SAS) and Self-Rating Depression Scale (SDS), respectively (Zung, 1971; Zung, 1965). Each scale contains 20 items scored from 1 to 4, yielding a raw total score of 20–80. In accordance with standard scoring procedures, raw scores will be multiplied by 1.25 to obtain index scores ranging from 25 to 100. Higher scores indicate greater symptom severity.

Gastrointestinal symptoms will be assessed using the Gastrointestinal Symptom Rating Scale (GSRS) (Revicki et al., 1998). The GSRS comprises 15 items scored on a 7-point Likert scale and evaluates the severity of common gastrointestinal symptoms, including reflux, abdominal pain, indigestion, diarrhea, and constipation-related symptoms. Higher scores indicate more severe gastrointestinal symptoms.

Bowel function will be assessed using the Bristol Stool Form Scale (BSFS) and a stool frequency diary (Lewis and Heaton, 1997). The BSFS classifies stool form into seven categories, with types 1–2 indicating constipation and types 3–5 indicating normal stool form.

Handgrip strength (HGS) testing will be used to assess muscle strength and fatigability (Popkirov, 2025). Participants will perform 10 consecutive maximal grips using a hand dynamometer and will repeat the same procedure 60 min later. For each session, maximal force (Fmax) and mean force (Fmean), expressed in kilograms, will be recorded. The first session values will be denoted as Fmax1 and Fmean1, and the second session values as Fmax2 and Fmean2. The fatigue ratio will be calculated as Fmax/Fmean, with higher values indicating a greater decline in force across repeated contractions (Jäkel et al., 2021).

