In summary, Tuina may represent a low-risk and adaptable option for CFS, but its therapeutic effects and underlying mechanisms remain insufficiently characterized. This trial is designed to evaluate the efficacy of Tuina for reducing fatigue and improving related symptoms in patients with CFS. Gastrointestinal symptoms will be assessed as an important clinical and mechanistic domain rather than as an entry criterion. In addition, multimodal assessments, including functional MRI, magnetic resonance spectroscopy, metabolomic analysis, and metagenomic profiling, will be used to explore potential gut-brain mechanisms, with particular attention to associations among gut microbial features, tryptophan-related metabolites, and brain functional characteristics in CFS.

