### Study design

3.1

This study is a multicenter, parallel-group, open-label randomized controlled trial with blinded outcome assessors and statisticians. The trial is organized with Shuguang Hospital Affiliated to Shanghai University of Traditional Chinese Medicine serving as the primary study center and Yueyang Hospital of Integrated Traditional Chinese and Western Medicine participating as an additional recruiting center. The study protocol has been approved by the Ethics Committee of Shuguang Hospital Affiliated to Shanghai University of Traditional Chinese Medicine and by the Ethics Committee of Yueyang Hospital of Integrated Traditional Chinese and Western Medicine, and has been registered at the International Traditional Medicine Clinical Trial Registry (ITMCTR2025002204). Participants will be randomly allocated in a 1:1 ratio to either the Tuina group or the control group (standardized usual care), and both groups will receive their assigned interventions for 8 weeks. Outcome assessments will be conducted at baseline, week 4, week 8 (end of treatment), and 12 and 24 weeks after the end of treatment. To improve participant retention and acknowledge trial participation, participants in the control group will be offered two Tuina sessions after completion of the final 24-week follow-up assessment. This protocol was developed in accordance with the Standard Protocol Items: Recommendations for Interventional Trials (SPIRIT) statement (Chan et al., 2025). The study flowchart is presented in Figure 1, and the detailed schedule of enrollment, interventions, and assessments is shown in Table 1.

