### Eligibility criteria

3.3

Inclusion criteria:

1) The diagnostic criteria of potential participants refer to the 2015 Institute of Medicine (IOM) criteria for CFS (Clayton, 2015):

Substantial reduction or impairment in activity level with fatigue >6 months,Post-exertional malaise (PEM),Unrefreshing sleep,One of the symptoms: cognitive impairment or orthostatic intolerance.

2) Age 20–60 years, of either sex, and right-handed.3) No use within the past month of treatments considered likely to affect the primary outcomes or mechanistic assessments, including herbal formulas, acupuncture, other related non-pharmacological therapies, and antibiotics, probiotics, or prebiotics.4) Able to communicate and complete study questionnaires, and willing to accept randomization and provide written informed consent.

Exclusion criteria:

Fatigue symptoms that do not lead to a substantial reduction in the capacity for work, education, social and recreational activities, or activities of daily living.Severe comorbid conditions, including decompensated cardiac, cerebrovascular, hepatic or renal disease, malignancy, active infection, or neurological disorders.Severe psychiatric disorder, or severe depressive symptoms requiring immediate treatment, as indicated by a Self-Rating Depression Scale score ≥63 or clinical judgment.Pregnancy, planned pregnancy or lactation.Contraindications to MRI, such as pacemaker, neurostimulator, metallic implants or insulin pumps, in participants enrolled in the imaging substudy.Morbid obesity, defined as BMI > 45 kg/m^2^.Any other condition that, in the opinion of the investigator, would contraindicate participation or continuation in the trial, or would provide a more likely alternative clinical explanation for fatigue.

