### Statistical analysis

3.9

Statistical analyses will be performed using SPSS version 26.0 (IBM Corp., Armonk, NY, USA). Baseline characteristics will be summarized as mean (SD) or median (IQR) for continuous variables and as number (%) for categorical variables, as appropriate. Longitudinal outcomes will be analyzed using linear mixed-effects models including fixed effects for group, time, and group-by-time interaction. The models will be adjusted for baseline outcome values, study center, and sex, with additional prespecified covariates included where appropriate. For the primary outcome analysis, baseline FS-14 score will be included as a covariate. Secondary clinical outcomes will be interpreted with consideration of multiplicity, and exploratory omics and imaging analyses will be interpreted as hypothesis-generating. All tests will be two-sided, and a *p* value <0.05 will be considered statistically significant. The primary efficacy analysis will follow the intention-to-treat principle. A per-protocol analysis will be conducted as a sensitivity analysis. The primary comparison will be the between-group difference in change in FS-14 total score from baseline to week 8, estimated from the mixed-effects model. Missing data will be handled under the missing-at-random assumption inherent to mixed-effects models, and additional sensitivity analyses will be conducted if warranted. Because this is a multicenter trial, study center will be included in the analysis model to account for potential between-center variability. All statistical analyses will be performed with group allocation concealed until database lock. The full trial protocol is provided in this article and its online Supplementary materials.

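### Bristol stool type is normal in the middle of its scale, but section 3.9 puts it under a linear-mean model, where improvements at the two ends offset each other partly or, if balanced, fully

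*Protocol article*

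**What the plan says.** Section 3.7.2 of the protocol article lists bowel function among the secondary outcomes: "Bowel function will be assessed using the Bristol Stool Form Scale (BSFS) and a stool frequency diary". It describes the scale by class: "The BSFS classifies stool form into seven categories, with types 1–2 indicating constipation and types 3–5 indicating normal stool form". Types 6–7 receive no label; by elimination they are the other abnormal end.

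Table 1 schedules the Bristol scale at weeks 0, 4 and 8 and at both follow-up visits, in line with section 3.1: "Outcome assessments will be conducted at baseline, week 4, week 8 (end of treatment), and 12 and 24 weeks after the end of treatment". It is therefore a longitudinal outcome.

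Section 3.9 states the analysis: "Longitudinal outcomes will be analyzed using linear mixed-effects models including fixed effects for group, time, and group-by-time interaction". On covariates it adds: "The models will be adjusted for baseline outcome values, study center, and sex, with additional prespecified covariates included where appropriate". No exception is made for any outcome, and no baseline-by-group term is named.

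On the population, the Introduction says: "Gastrointestinal symptoms will be assessed as an important clinical and mechanistic domain rather than as an entry criterion".

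**The concern.** A linear model compares group means, and a difference in means is interpretable only if higher, or lower, is consistently better. For the SF-36, PSQI, pain scale, SAS, SDS and GSRS the article states such a direction. For stool type it states none, and on the raw 1–7 number none exists: by the article's own classes, a rise from type 2 is an improvement and a rise from type 5 is not.

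With unselected bowel patterns the sample may hold both kinds of abnormal stool. That both matter to the trial is clear from the GSRS, described as "including reflux, abdominal pain, indigestion, diarrhea, and constipation-related symptoms". Improvement at one end raises mean type and improvement at the other lowers it. Bowel function is a named secondary objective (section 2.2), so what is at stake is whether the result for this outcome can be read at all.

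**Working it through.** **Inputs from the article.** Stool classes (3.7.2); five visits (Table 1); linear mixed model with baseline as a covariate (3.9); 66 evaluable per group and two-sided alpha 0.05 (3.4).

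**Inputs assumed.** The article gives no baseline distribution of stool types and no expected effect on them. Assume 60% abnormal at baseline, no change in controls, and half of each abnormal class reaching type 4 under Tuina. The split between constipated and loose is varied.

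**Step 1, the plan's own figure.** n = 2 × (1.96 + 0.842)² × 3.28² / 1.60² = 2 × 7.85 × 10.76 / 2.56 ≈ 66 per group; 66 / 0.80 = 82.5, rounded up to 83, total 166. The stated sample size reproduces. It concerns FS-14 only and supplies just the group size used in step 4.

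**Step 2, direction.** A move from type 2 to 3 enters the normal range; a move from type 5 to 6 leaves it. Both add +1 to the mean.

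**Step 3, offset.** Let c and l be the constipated and loose shares, r the fraction normalising and d the distance from each end to type 4.

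- Change in mean type = r × d × (c − l)
- Change in share with normal form = r × (c + l)

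The mean sees the difference between the two ends; the proportion sees their sum. With abnormal stools averaging types 1.5 and 6.5 (d = 2.5) and r = 0.5:

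- 30%/30%: mean change 0.15 × 2.5 − 0.15 × 2.5 = 0; normal form 40% to 70%.
- 40%/20%: mean change 0.20 × 2.5 − 0.10 × 2.5 = +0.25; normal form 40% to 70%.
- 60%/0%: mean change 0.30 × 2.5 = +0.75; normal form 40% to 70%.

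**Step 4, power at 66 per group.** This uses a separate, milder layout with stools at types 2, 4 and 6 (d = 2). Power for the mean is Φ(Δ/SE − 1.96) + Φ(−Δ/SE − 1.96), with SE = SD × √(2/66) and the SD averaged over the two arms' variances. For 40%/20%: Δ = 0.5 × 2 × 0.2 = 0.20, SD = 1.30, SE = 0.226, power 14%. The comparison is a two-proportion test of 70% against 40%.

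| Constipated / loose | Difference in mean type | Power, mean type | Power, normal form |
|---|---|---|---|
| 30% / 30% | 0.00 | 5% | 94% |
| 35% / 25% | 0.10 | 7% | 94% |
| 40% / 20% | 0.20 | 14% | 94% |
| 45% / 15% | 0.30 | 28% | 94% |
| 50% / 10% | 0.40 | 49% | 94% |
| 60% / 0% | 0.60 | 95% | 94% |

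**Step 5, baseline adjustment.** The table omits it. An additive baseline covariate can reduce residual variance, so the intermediate power figures could be higher under the planned model. It does not change the expected difference under randomisation, so the offset in step 3 remains.

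**The case against.** The strongest reply is that the article never says mean stool type is the endpoint. Section 3.9 speaks of longitudinal outcomes without the word all, and section 3.7.2 describes the scale by classes, which suits a derived categorical endpoint. The article refers to prespecified analysis plans and to online supplementary materials that are not at hand, and either might define one. That possibility stands and limits confidence. It does not remove the point: the published rule is unqualified, this outcome falls under it, and a supplement using a proportion would depart from it.

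A second reply is that the sizes are assumed. That also stands. A reader might infer that a real benefit will come out as zero. The documents do not support this: full cancellation needs balanced improvement at both ends, and the last row of the table shows no loss when all abnormal stools are constipated.

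Three further inferences go too far. The stool-frequency diary might seem to share the fault, but the article gives it no normal range or score and Table 1 has no row for it. The plan might seem set to count looser stools as a benefit, but it assigns no direction of benefit here. Finally, the trial might seem blind to bowel improvement, but the GSRS covers both diarrhea and constipation at the same five visits, with higher always worse.

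**Conclusion.** The concern holds in a limited form. Applied as written, the rule in section 3.9 yields a mean stool type with no direction of benefit, in a sample not selected by bowel pattern. Where both ends improve, part of the effect is lost from the mean; where they balance, all of it is. In the illustrations a 30-point rise in normal form appears as a mean change anywhere from 0 to +0.75 type, depending only on the mix.

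This rests on three things: that the linear rule applies to this scale because no exception is named, that types 6–7 are the other abnormal end, and that both ends occur among participants. The effect is confined to one secondary outcome. The primary FS-14 analysis and the sample size are unaffected. It should be corrected, but it does not threaten the trial's main conclusion.

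**What to change.** In section 3.7.2, label types 6–7 explicitly and define the endpoint as normal form (types 3–5) versus abnormal form (types 1–2 or 6–7). In section 3.9, exempt the Bristol scale from the linear-mean rule and analyse this endpoint with a logistic mixed model or GEE, adjusted for baseline class and centre. Report constipation and loose stool separately as support, so that the source of any change is visible.

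The cost is about two sentences, with no new data. Dichotomising discards movement within a class. Distance from the normal range, or analysis by baseline stool type, are acceptable alternatives if that loss matters. Whichever is chosen should be fixed before unblinding, and any supplement or analysis plan that already defines the endpoint should be brought into line with section 3.9.

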#### Exploratory mechanistic outcomes

3.7.3

Exploratory mechanistic assessments will be conducted according to predefined sampling frameworks. Plasma metabolomic analyses and stool metagenomic analyses will be attempted in all randomized participants who provide usable biological samples at the specified time points (baseline and week 8). Resting-state fMRI and MRS will be conducted in a predefined imaging substudy composed of participants who provide additional consent and have no MRI contraindications. Participation in the imaging substudy is optional and is not required for enrollment in the main randomized trial. We expect that approximately 60 participants of the full cohort will participate in the imaging substudy, depending on consent, eligibility, and scanner availability. These exploratory mechanistic assessments are not formally powered for confirmatory hypothesis testing and are intended to estimate effect sizes, characterize biological patterns, and generate hypotheses for future studies.

The rationale for each exploratory domain is described below. First, disturbances in tryptophan metabolism, particularly within the kynurenine pathway, have been implicated in immune activation, neuroactive metabolite imbalance, and fatigue-related symptoms. Alterations in the KYN/Trp ratio may reflect inflammatory signaling and indoleamine 2,3-dioxygenase activity (Muneer, 2020). Recent CFS studies have suggested abnormal tryptophan catabolism and increased kynurenine production, indicating that tryptophan metabolites may link peripheral dysregulation with central symptoms such as cognitive dysfunction and sleep disturbance (Groven et al., 2021; Hsu et al., 2025). Accordingly, plasma and stool samples will be collected to quantify tryptophan and its downstream metabolites using targeted liquid chromatography-mass spectrometry (LC–MS) (Desmons et al., 2022). Samples will be processed according to standardized laboratory procedures, as described in the online Supplementary materials.

Second, gut microbiota will be evaluated as an exploratory outcome. Growing evidence supports an association between CFS and gut microbial dysbiosis, with reported alterations in microbial composition, barrier-related processes, and microbially mediated metabolites (Wang et al., 2024; Prylińska-Jaśkowiak et al., 2025; El-Sehrawy et al., 2025; Stallmach et al., 2024). However, current evidence remains insufficient to establish a causal role of the gut microbiota in CFS pathogenesis, underscoring the need for integrative clinical studies linking microbial measures with symptoms and brain-based outcomes. Because Tuina is applied over the abdomen and paraspinal regions and may influence autonomic regulation and gastrointestinal function, stool metagenomic profiling will be used to explore whether the intervention is associated with changes in gut microbial composition and function. Stool samples will be collected at predefined time points, and metagenomic sequencing will be conducted using standardized procedures. Detailed methods for library preparation, sequencing, and bioinformatic analysis are provided in the online Supplementary materials.

Third, fMRI and MRS will be used to explore potential central mechanisms of Tuina in CFS. Resting-state fMRI studies in CFS have reported altered functional connectivity within and between large-scale brain networks related to fatigue, pain, and cognitive symptoms (Su et al., 2023; Boissoneault et al., 2016). Proton MRS studies have also identified abnormalities in brain metabolites associated with energy metabolism and neuroinflammatory processes (Godlewska et al., 2025; Mueller et al., 2020). Magnetic resonance spectroscopy offers an *in vivo* window into neurochemical processes potentially relevant to fatigue-related disorders. Recent ultra-high-field MRS work in CFS has identified elevated anterior cingulate lactate, consistent with energetic stress and altered mitochondrial-related metabolism, supporting the inclusion of MRS as a complementary modality alongside rs-fMRI in mechanistic studies of CFS (Godlewska et al., 2025). In this study, resting-state fMRI and MRS will be acquired on a 3.0 T Siemens scanner using standardized protocols. Functional imaging analyses will focus on amplitude of low-frequency fluctuation, regional homogeneity, and functional connectivity, while MRS analyses will examine region-specific metabolite profiles in predefined brain regions of interest. Detailed acquisition parameters, preprocessing procedures, motion-control criteria, and region-of-interest definitions are provided in the online Supplementary materials.

